### Process evaluation, resource data and costs

All participants complete a short telephone questionnaire during week 6 of the intervention with acceptability questions on pilot-trial processes, any risks/safety issues and engagement with the intervention. Key issues are being further explored in qualitative interviews. The intervention delivery team records views on feasibility, experience of delivering the intervention and suggestions for improving study processes in a reflective diary. We are collecting resource data and assessing the feasibility of collecting data required for a cost-effectiveness analysis in a future trial, following current health economic analysis guidelines for pilot intervention studies.^40^ We have conducted a literature review to identify approaches and methods used for economic evaluations in similar studies and have identified potential costs and outcomes using a cost-consequences analysis framework. We have developed a conceptual model to visually represent the research problem and have used this to identify relevant resources used in the provision of the intervention including NRT type, dose and frequency; the staff grade and time spent providing telephone support. We have developed a resource use form to collect this data. 

### Data analysis plan

Descriptive data analyses will be performed to address the feasibility objectives. Child saliva samples will be processed for salivary cotinine by a specialist, accredited laboratory. The research team will analyse data from the air quality monitors. We will report the percentage of participants that return a valid (sufficient saliva) sample through self-collection, and the level of agreement between the self-collected and researcher-collected salivary cotinine values at baseline to determine the suitability of self-collection of these samples. Analysis will also include pre/post changes (paired t-test) in both child’s salivary cotinine and PM_2.5_ levels to provide preliminary data on intervention effectiveness and difference between the intervention and control arms of the study. Data on variability in these objective measures will also help calculate suitable sample size for the future trial. The qualitative data from the 6-week process evaluation questionnaire will be analysed using content analysis. All qualitative interviews will be recorded with participant permission, transcribed, anonymised and analysed using the framework approach. Transcripts and recordings will be stored securely and destroyed in line with University of Stirling procedures, taking account of General Data Protection Regulation. The health economics and resource use data will be assessed for completeness, to test the process of data collection and the mean cost of both study arms estimated. We will assess suitable outcomes and identify key drivers of uncertainty for any future economic evaluation in a large-scale trial. We will consider the suitability of data to inform a cost-consequence analysis (particularly suitable for public health interventions with multiple possible benefits) and conduct this analysis, to provide information on where further focus might be beneficial in a future definitive trial. 

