**Methods and analysis:**

100 participants are being recruited through existing National Health Service (NHS) Lanarkshire initiatives and social media. Parents/carers who are at least 18 years old, smoke in the home and care for one or more children aged 0–16 years are eligible to take part. Participants are randomised to either the intervention (Group A) or control (Group B) arm. Group A receives NRT posted to their home for 12 weeks free of charge, alongside fortnightly telephone calls and materials to support them in reducing children’s exposure to SHS. Group B is signposted to the Scottish Government’s ‘Take it Right Outside’ website which provides interactive advice on creating a smoke-free home. To quantify the child’s exposure to SHS, participants instal an air quality monitor to measure fine particulate matter (PM_2.5_) concentrations in their living room for 7 days at baseline and 12-week follow-up and/or collect and post saliva samples from their youngest child (age 5 or over) for cotinine analysis. Qualitative interviews explore intervention experience, NRT use and adherence and changes to home-smoking behaviours/smoking-related expenditure. Descriptive data analyses will be performed to address the feasibility of recruitment, randomisation, retention and adherence, data collection and intervention delivery. Analysis will also include pre/post changes (paired t-test) in both child’s salivary cotinine and PM_2.5_ levels to provide preliminary data on intervention effectiveness and difference between the intervention and control arms of the study. Health economics and resource use data will be collected and assessed for completeness, to test the process of data collection and estimate mean cost of both study arms.

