Following methods used in the annual health survey in England for collection of child saliva samples, if parents choose this option, they are required to provide written consent for the collection of saliva samples from their youngest child aged 5 or over. A copy of the completed consent form is posted to all participants. We provide each participant with an age-appropriate information sheet by post for them to share and discuss with their child in advance of a prearranged home visit from a member of the NHS intervention delivery team. During this visit, the child is required to assent to the sample collection for it to proceed. The process for gaining assent from the child also follows those used in the annual health survey in England. Parents are required to give fully informed consent. Assent from children indicates that they have been given an age-appropriate explanation that they can understand (even if not as comprehensive as for an adult), and that the child is happy for the procedure to go ahead.^33^ Children are not required to sign anything, but the NHS Lanarkshire intervention delivery team member signs an ID form to confirm the child’s assent has been obtained during the home visit. With permission, (and in the case of parents, if they choose to have air quality measured in their home), the team member also instals an air quality monitor during this visit, to measure PM_2.5_ levels in the home for 1 week.

A suitable date/time is agreed during this home visit for the same team member to telephone each participant after 1 week, to initiate intervention delivery. Participants are randomised (1:1) to either the intervention (Group A) or control (Group B) arm prior to this telephone call. If more than one individual from the same family participates in the study, each family member is allocated to the same study arm.

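### The only test named for effectiveness and the between-arm difference is a paired t-test of pre/post change, which estimates neither

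*Protocol article*

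**What the plan says.** The Data analysis plan separates two kinds of analysis. The feasibility objectives, which are primary, are handled descriptively: "Descriptive data analyses will be performed to address the feasibility objectives". For the two objective exposure measures it then says: "Analysis will also include pre/post changes (paired t-test) in both child’s salivary cotinine and PM_2.5_ levels to provide preliminary data on intervention effectiveness". The sentence goes on to give a second purpose, the "difference between the intervention and control arms of the study". The abstract (Methods and analysis) repeats the statement: "Analysis will also include pre/post changes (paired t-test) in both child’s salivary cotinine and PM_2.5_ levels". The article names no two-sample test, between-arm estimate, confidence interval or baseline-adjusted model.

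The design is a parallel-group randomised trial: "Participants are randomised (1:1) to either the intervention (Group A) or control (Group B) arm prior to this telephone call". Where several relatives take part, "each family member is allocated to the same study arm". The Sample size section aims for 100 recruits, to leave about 35 per arm after 30% drop-out. Control participants are signposted to official smoke-free-home advice (Control arm). Under Objective SHS measures, child cotinine is the intended primary outcome of the definitive trial and PM2.5 is a possible alternative.

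**The concern.** One method is named and two purposes are attached to it. A paired t-test compares baseline with follow-up in the same units. Run separately in each arm, it gives the mean change in that arm. Run on both arms pooled, it gives the mean change overall and ignores allocation. Neither is a treatment effect.

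Change over 12 weeks also contains things unrelated to the posted NRT and calls: season, regression to the mean, behaviour altered by being monitored and, in Group B, the advice that controls receive. Some movement in both arms is therefore plausible by design.

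At stake is how the pilot's published effectiveness result is read. A significant fall in Group A beside a non-significant fall in Group B invites the conclusion that the intervention worked, yet that pattern is common when both arms change equally. Because these are the candidate primary outcomes of the definitive trial, the pilot should report the quantity that trial will estimate.

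**Working it through.** **The plan's own figure.** 35 / (1 − 0.30) = 50 per arm, so 100 in total. The recruitment target reproduces. The article gives no alpha, power, effect size or SD, so there is no power figure to check.

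**What the named test estimates.** Write the change in arm A as shared change + treatment effect, and the change in arm B as shared change alone. A paired test in A targets shared change + effect. A pooled paired test with equal arms targets shared change + half the effect. Only the difference between arms removes the shared part.

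**How misleading an arm-by-arm reading could be.** Inputs:
- n = 35 pairs per arm (Sample size).
- Assumed, because the article gives none: two-sided 5% tests, no treatment effect, independent arms, and the same true reduction of d SDs of change in both arms.

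In each arm the paired t statistic is noncentral t with 34 df and noncentrality d√35. Let p be the probability of significance in either direction and p₊ the probability of a significant reduction. Then P(significant reduction in A, B not significant) = p₊ × (1 − p). For example:
- d = 0: 0.025 × 0.95 = 0.024.
- d = 0.3: 0.407 × 0.593 = 0.241.

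| Shared change d | P(A significant) | P(A significant reduction, B not) |
|---|---|---|
| 0 | 5.0% | 2.4% |
| 0.2 | 21.0% | 16.5% |
| 0.3 | 40.7% | 24.1% |
| 0.33 | 47.5% | 24.9% |
| 0.4 | 63.3% | 23.2% |
| 0.5 | 82.0% | 14.8% |
| 0.6 | 93.2% | 6.4% |

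The product peaks near 25%, where p is about one half. A two-sample test of the changes favours A falsely in 2.5% of trials whatever d is. A simulation of 20,000 trials agreed. At d = 0.33 and 0.4 the A-only pattern occurred in 24.6% and 23.5%, and the two-sample test rejected (both directions) in 5.0% and 5.1%.

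**Fewer pairs.** Saliva and air monitoring are offered as an and/or choice, and saliva is not taken from children under 5 or by relatives caring in their own home. Either measure may therefore have fewer than 35 pairs per arm. At d = 0.2, 0.4 and 0.6 the A-only pattern occurs in 13.3%, 25.0% and 14.7% with 25 pairs per arm, and in 10.8%, 23.0% and 22.1% with 18. The peak stays near 25% and moves to a larger d.

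**Precision of a between-arm estimate.** With 35 per arm, outcome SD 1 and an assumed baseline/follow-up correlation r, the approximate 95% CI half-width is 1.96√(2(1 − r²)/35) for ANCOVA and 1.96√(4(1 − r)/35) for the difference in changes.

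| r | ANCOVA | Difference in changes |
|---|---|---|
| 0.3 | 0.447 SD | 0.554 SD |
| 0.5 | 0.406 SD | 0.469 SD |
| 0.7 | 0.335 SD | 0.363 SD |

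These widths treat participants as independent, so they are somewhat optimistic if families contribute more than one member.

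**The case against.** The strongest defence is grammatical. The parenthesis naming the test sits beside the pre/post changes, and the arm difference can be read as a separate item whose method is left to a fuller document. That has force: a reader might infer that the plan throws away the randomised comparison, and the text does not support this, because the arm difference is an announced aim. It is also not stated whether the paired test is per arm or pooled. But on this reading the paired test is still the method given for intervention effectiveness, which a before-after contrast cannot show.

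Two further inferences fail. A reader might suppose that the t-test result drives the decision to proceed. The four criteria in Table 1 are recruitment, completed follow-up, NRT use with call engagement, and safety, and the text after the table adds the process questionnaire, interviews and emerging evidence. No exposure result is listed. A reader might also suppose that the future sample size would be distorted. The Data analysis plan links that calculation to the variability of the measures, which does not depend on the test chosen.

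It is also fair that the shared change is assumed, that the rates near 25% are the top of a range starting at 2.4%, and that the plan nowhere says it will compare two p-values. Finally, ANCOVA is not the only remedy: a simple comparison of changes between arms would also answer the point. ANCOVA is preferred for precision.

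**Conclusion.** The point stands in a limited form. A stated method does not fit its stated purpose in both the abstract and the Data analysis plan, and this holds whether the paired test is run per arm or pooled. The possible cost is a spurious A-only signal in between 2.4% and about 25% of trials with no treatment effect, against 2.5% for a two-sample test. That range rests on two-sided 5% tests, 35 pairs per arm, an equal change in both arms of 0 to 0.6 SD, and a reader who compares the arms by significance. The primary objectives are analysed descriptively, the exposure results are called preliminary, and they enter neither the progression criteria nor, beyond their variability, the future sample size. It should be corrected before analysis, but it does not threaten the pilot's main purpose.

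**What to change.** Replace the sentence in the Data analysis plan, and its counterpart in the abstract, with a between-arm estimate. For each of child cotinine and PM2.5, regress the follow-up value on arm and baseline value (ANCOVA), analyse participants with data as allocated, and report the adjusted difference with a 95% CI, labelled exploratory. Allow for relatives placed in the same arm, for example by keeping one record per home or child or by using cluster-robust standard errors. Show within-arm changes as descriptive summaries only, without tests. Baseline values are already collected, so this needs no new data or participants and leaves the target of 100 unchanged. The cost is a sentence or two of text and a little more analysis work.

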### Ethics and dissemination

The study obtained ethical approval from the West of Scotland Research Ethics Service 3 (15 December 2023, ref 23/WS/0153; 13 December 2024, ref AM01). The study protocol is registered with the ISRCTN registry (ISRCTN79307718). The protocol and this manuscript both align with recommendations^42^ for using the SPIRIT (Standard Protocol Items: Recommendations for Interventional Trials)^43^ and CONSORT (Consolidated Standards of Reporting Trials)^44 45^ statement extension for reporting pilot trials. The findings will be relevant to a wide range of audiences interested in tobacco control, including researchers working in behavioural sciences and public health, graduate and postgraduate students, health professionals, advocacy organisations, policymakers and health economists. The primary means of disseminating study findings to these audiences will be publication of findings in peer-reviewed, open access scientific journals. The results will also be disseminated at local, national and international meetings and conferences on tobacco control. We will also disseminate a summary of study findings to study participants. Findings will inform new approaches that are timely and important, providing valuable evidence to help reduce children’s exposure to SHS in the home in Scotland and elsewhere.
